# Local Number of Subjects

- 1. Indicate the total number of subjects that will be enrolled or records that will be reviewed locally.

Response:

No recruitment or enrollment proposed by the Buffalo investigators.

- 1. If applicable, indicate how many subjects you expect to screen to reach your target sample (i.e. your screen failure rate).

Response:

No screening, recruitment.

- 1. Justify the feasibility of recruiting the proposed number of eligible subjects within the anticipated recruitment period. For example, how many potential subjects do you have access to? What percentage of those potential subjects do you need to recruit?

Response:

No recruitment.

# Inclusion and Exclusion Criteria

- 1. Describe the criteria that define who will be **included** in your final study sample.

NOTE: This may be done in bullet point fashion.

Response:

Not applicable. No patient recruitment is proposed. This is analysis of samples that will be collected by [name] group at the University of Iowa.

- 1. Describe the criteria that define who will be **excluded** from your final study sample.

NOTE: This may be done in bullet point fashion.

Response:

Not applicable. No patient recruitment is proposed. This is analysis of samples that will be collected by [name] group in Iowa

- 1. Indicate specifically whether you will include any of the following special populations in your study using the checkboxes below.

**NOTE: Members of special populations may not be targeted for enrollment in your study unless you indicate this in your inclusion criteria.**

Response:

Adults unable to consent

Individuals who are not yet adults (infants, children, teenagers)

Pregnant women

Prisoners

- 1. Indicate whether you will include non-English speaking individuals in your study. **Provide justification if you will exclude non-English speaking individuals.**

In order to meet one of the primary ethical principles of equitable selection of subjects, non-English speaking individuals may **not** be routinely excluded from research as a matter of convenience.

In cases where the research is of therapeutic intent or is designed to investigate areas that would necessarily require certain populations who may not speak English, the researcher is required to make efforts to recruit and include non-English speaking individuals. However, there are studies in which it would be reasonable to limit subjects to those who speak English. Some examples include pilot studies, small unfunded studies with validated instruments not available in other languages, studies with numerous questionnaires, and some non-therapeutic studies which offer no direct benefit.

Response:

No recruitment

# Vulnerable Populations

If the research involves special populations that are considered vulnerable, **describe the safeguards included to protect their rights and welfare.**

NOTE: You should refer to the appropriate checklists, referenced below, to ensure you have provided adequate detail regarding safeguards and protections. You do not, however, need to provide these checklists to the IRB.

- 1. For research that involves **pregnant women,** safeguards include:
     NOTE CHECKLIST: Pregnant Women (HRP-412)

Response:

✔**N/A**: This research does not involve pregnant women.

- 1. For research that involves **neonates of uncertain viability or non-viable neonates,** safeguards include:

NOTE CHECKLISTS: Non-Viable Neonates (HRP-413), or Neonates of Uncertain Viability (HRP-414)

Response:

✔**N/A:** This research does not involve non-viable neonates or neonates of uncertain viability.

- 1. For research that involves **prisoners**, safeguards include:

NOTE CHECKLIST: Prisoners (HRP-415)

Response:

✔**N/A:** This research does not involve prisoners.

- 1. For research that involves **persons who have not attained the legal age for consent to treatments or procedures involved in the research (“children”)**, safeguards include:
     NOTE CHECKLIST: Children (HRP-416)

Response:

✔**N/A:** This research does not involve persons who have not attained the legal age for consent to treatments or procedures (“children”).

- 1. For research that involves **cognitively impaired adults**, safeguards include:

NOTE CHECKLIST: Cognitively Impaired Adults (HRP-417)

Response:

✔**N/A:** This research does not involve cognitively impaired adults.

- 1. Consider if other specifically targeted populations such as students, employees of a specific firm, or educationally or economically disadvantaged persons are vulnerable. **Provide information regarding their safeguards and protections, including safeguards to eliminate coercion or undue influence.**

Response:

# Eligibility Screening

- 1. Describe **screening procedures** for determining subjects’ eligibility. Screening refers to determining if prospective participants meet inclusion and exclusion criteria.

[figure not shown]
Include all relevant screening documents with your submission (e.g. screening protocol, script, questionnaire).

Response:

✔**N/A:** There is no screening as part of this protocol.

# Recruitment Methods

**N/A:** This is a records review only, and subjects will not be recruited. NOTE: If you select this option, please make sure that all records review procedures and inclusion/exclusion screening are adequately described in other sections.

- 1. Describe when, where, and how potential subjects will be recruited.

NOTE: Recruitment refers to how you are identifying potential participants and introducing them to the study. Include specific methods you will use (e.g. searching charts for specific ICD code numbers, Research Participant Groups, posted advertisements, etc.).

Response:

Not applicable. No recruitment as part of this protocol.

- 1. Describe how you will protect the privacy interests of prospective subjects during the recruitment process.

NOTE: Privacy refers to an individual’s right to control access to him or herself.

Response:

Not applicable. No recruitment.

- 1. Identify any materials that will be used to recruit subjects.

NOTE: Examples include scripts for telephone calls, in person announcements / presentations, email invitations.

[figure not shown]
For advertisements, include the final copy of printed advertisements with your submission. When advertisements are taped for broadcast, attach the final audio/video tape. NOTE: You may submit the wording of the advertisement prior to taping to ensure there will be no IRB-required revisions, provided the IRB also reviews and approves the final version.

Response:

Not applicable. No recruitment materials.

# Procedures Involved

- 1. Provide a description of **all research procedures or activities** being performed and when they are performed once a subject is screened and determined to be eligible. Provide as much detail as possible.

NOTE: This should serve as a blueprint for your study and include enough detail so that another investigator could pick up your protocol and replicate the research. For studies that have multiple or complex visits or procedures, consider the addition of a schedule of events table in in your response.

Response:

No procedures will be conducted as part of this study. All recruitment, procedures, interventions sample collection are being conducted by [name] team at the University at Iowa. The samples and data collection from the first study is complete and the second study is ongoing. Patients have provided informed consent for use of the data and samples for research for both studies to [name] team at the University at Iowa. We will receive the samples by overnight delivery (e.g., UPS, FedEx etc.) on dry ice.

- 1. Describe what data will be collected.

NOTE: For studies with multiple data collection points or long-term follow up, consider the addition of a schedule or table in your response.

Response:

No procedures.

- 1. List any instruments or measurement tools used to collect data (e.g. questionnaire, interview guide, validated instrument, data collection form).

[figure not shown]

     Include copies of these documents with your submission.

Response:

No interventions or procedures on patients for this project. Previously collected blood samples will be analyzed using instruments in [name] laboratory.

- 1. Describe any source records that will be used to collect data about subjects (e.g. school records, electronic medical records).

Response:

This is analysis of samples and data that will be collected by [name] group in Iowa. We will receive clinical, demographic and fatigue outcome data from our Iowa collaborators. The Buffalo investigators will receive only de-identified samples. Identifiers are not needed for our study. [name] and her medical team at Iowa have identifiers but we will work with de-identified data. Raw charts will not be received. Relevant data from the charts will be summarized in files by [name] team. The de-identified data will be received electronically.

- 1. Indicate whether or not **individual** subject results, such as results of investigational diagnostic tests, genetic tests, or incidental findings will be shared with subjects or others (e.g., the subject’s primary care physician) and if so, describe how these will be shared.

Response:

The individual subjects results will not be shared. Aggregate statistical findings will be published in peer-reviewed literature and professional conferences.

- 1. Indicate whether or not **study** results will be shared with subjects or others, and if so, describe how these will be shared.

Response:

Study results will be published in the literature and shared with sponsors/funding agencies. Results may be shared with qualified scientists involved in MS research as part of research collaborations.

# Study Timelines

- 1. Describe the anticipated duration needed to enroll all study subjects.

Response:

No enrollment.

- 1. Describe the duration of an individual subject’s participation in the study. Include length of study visits, and overall study follow-up time.

Response:

No enrollment.

- 1. Describe the estimated duration for the investigators to complete this study (i.e. all data is collected and all analyses have been completed).

Response:

Approximately 5 years. Data acquisition will require 3 years and analysis will require 2 additional years.

# Setting

- 1. Describe all facilities/sites where you will be conducting research procedures. Include a description of the security and privacy of the facilities (e.g. locked facility, limited access, privacy barriers). Facility, department, and type of room are relevant. Do not abbreviate facility names.

NOTE: Examples of acceptable response may be: “A classroom setting in the Department of Psychology equipped with a computer with relevant survey administration software,” “The angiogram suite at Buffalo General Medical Center, a fully accredited tertiary care institution within New York State with badge access,” or, “Community Center meeting hall.”

Response:

A University research laboratory. All rooms have barriers and locks.

- 1. For research conducted outside of UB and its affiliates, describe:
- Site-specific regulations or customs affecting the research
- Local scientific and ethical review structure

NOTE: This question is referring to UB affiliated research taking place outside UB, i.e. research conducted in the community, school-based research, international research, etc. It is not referring to multi-site research. UB affiliated institutions include Kaleida Health, ECMC, and Roswell Park Cancer Institute.

Response:

✔**N/A:** This study is not conducted outside of UB or its affiliates.

# Community-Based Participatory Research

- 1. Describe involvement of the community in the design and conduct of the research.

NOTE: Community-Based Participatory Research (CBPR) is a collaborative approach to research that equitably involves all partners in the research process and recognizes the unique strengths that each brings. CBPR begins with a research topic of importance to the community, has the aim of combining knowledge with action and achieving social change to improve health outcomes and eliminate health disparities.

Response:

✔**N/A:** This study does not utilize CBPR.

- 1. Describe the composition and involvement of a community advisory board.

Response:

✔**N/A:** This study does not have a community advisory board.

**Describe other resources available to conduct the research.**

- 1. Describe the time and effort that the Principal Investigator and research staff will devote to conducting and completing the research.

NOTE: Examples include the percentage of Full Time Equivalents (FTE), hours per week. The question will elicit whether there are appropriate resources to conduct the research.

Response:

Drs. [name] and [name] will each devote 0.5 calendar months per year. Drs. [name] will devote 0.25 calendar months per year.

- 1. Describe the availability of medical or psychological resources that subjects might need as a result of anticipated consequences of the human research, if applicable.

NOTE: One example includes: on-call availability of a counselor or psychologist for a study that screens subjects for depression.

Response:

No recruitment.

- 1. Describe your process to ensure that all persons assisting with the research are adequately informed about the protocol, the research procedures, and their duties and functions.

Response:

No recruitment. The project proposal has been shared with all the investigators. The project proposal will be shared with all persons assisting with the research when the project is funded. Their immediate supervisors will inform them of their duties and functions.

# Other Approvals

- 1. Describe any approvals that will be obtained prior to commencing the research (e.g., school, external site, funding agency, laboratory, radiation safety, or biosafety).

Response:

✔**N/A:** This study does not require any other approvals.

# Provisions to Protect the Privacy Interests of Subjects

- 1. Describe how you will protect subjects’ privacy interests during the course of this research.

NOTE: Privacy refers to an individual’s right to control access to him or herself. Privacy applies to the person. Confidentiality refers to how data collected about individuals for the research will be protected by the researcher from release. Confidentiality applies to the data.

Examples of appropriate responses include: “participant only meets with a study coordinator in a classroom setting where no one can overhear”, or “the participant is reminded that they are free to refuse to answer any questions that they do not feel comfortable answering.”

Response:

- 1. Indicate how the research team is permitted to access any sources of information about the subjects.

NOTE: Examples of appropriate responses include: school permission for review of records, consent of the subject, HIPAA waiver. This question **does apply** to records reviews.

Response:

# Data Management and Analysis

- 1. Describe the data analysis plan, including any statistical procedures. This section applies to both quantitative and qualitative analysis.

Response:

The demographic, clinical and biomarker data will be centrally organized in a relational database (e.g., Access) and exported for statistical analysis. Range and consistency checks will be performed to identify errors. SPSS Statistics (IBM) will be used. We will assess descriptive statistics, distributions and pairwise correlations to inform analyses. A systematic hierarchical approach to analysis will be employed given the number of oxysterols, clinical and fatigue measures. Analyses will correct for multiple testing using the Benjamini-Hochberg method [20](#_ENREF_20).

Where necessary, clinical thresholds from the National Cholesterol Education Program Guidelines [32](#_ENREF_32) of HDL < 40, LDL-C ≥ 130, and TC ≥ 200 mg/dl will be used to create indicator variables for classifying subjects with low HDL-C, high LDL-C and high TC, respectively; hypercholesterolemia will be defined as TC ≥ 240 mg/dl. Appropriate regression analyses will be used for assessing associations of cholesterol biomarker and the clinical and fatigue variables (dependent variables). Count variables, e.g., relapse rate, will be analyzed with negative binomial regression. Ordinal regression will be used for EDSS.

Several clinically relevant questions will be addressed in the analyses. We expect the cholesterol profiles to differ between the Usual Diet phase vs. Swank Diet vs. Wahls’ Elimination Diet groups. The effects of diet on individual apolipoproteins, CRP and paraoxonase and other markers will also be investigated. Likewise, we will investigate whether oxysterol levels differ between the Usual Diet, Swank Diet and Wahls’ Diet groups? Given the longitudinal design we will also be able identify those oxysterols whose changes are associated with changes in lipid profile variables.

Since we hypothesize that decreased 24HCand increased 7KC are associated with greater neurodegeneration in MS, our primary analysis will evaluate the associations of changes in these oxysterols in the Usual Diet, Swank Diet and Wahls’ Elimination Diet groups. The interpretation framework was noted previously: 24HC is a marker of CNS cholesterol metabolism and 7KC is a marker of oxidative stress.

We will generally adopt the statistical framework and strategies used by Wahls’ et al. in their primary outcome analyses wherever appropriate. We have data on several key covariates that may require consideration. The repeated measures regression analyses will adjust for age and sex because cholesterolemia risk increases with age and is more frequent in males. We will also explore other covariate adjustments. For example, cholesterol profiles depend on body mass index (BMI), which we will adjust for.

- 1. If applicable, provide a power analysis.

NOTE: This may not apply to certain types of studies, including chart/records reviews, survey studies, or observational studies. This question is asked to elicit whether the investigator has an adequate sample size to achieve the study objectives and justify a conclusion.

Response:

Not applicable. No patient recruitment is planned.

- 1. Describe any procedures that will be used for quality control of collected data.

Response:

The inter-day and intra-day CVs for cholesterol biomarkers and apolipoproteins are < 5%. Our oxysterol assay has been validated in accordance with the FDA guidance for bioanalytical methods. The coefficient of variation (CV) was ≤ 8.7% 1. Range and consistency checks will be performed to identify errors in data entry. We will obtain descriptive statistics and assess distributions and pairwise correlations to inform analyses.

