We will systematically investigate the oxysterols 24-hydroxycholesterol (24HC), 27-hydroxycholesterol (27HC), 7α-hydroxycholesterol (7αHC) and 7-ketocholesterol (7KC) because they are potent transcription factor ligands and regulatory mediators of cholesterol and immune homeostasis. These oxysterols have been shown to modulate the interactions between immune cells and the vascular cells of the BBB and CNS pathophysiology.

**Specific Aim 1 >** Characterize the longitudinal changes in lipid profile occuring during the “Usual Diet Phase” and in the Swank Diet and Wahls’ Elimination Diet groups.

For this aim, a comprehensive lipid profile will be obtained. The profile will consist of: i) overall lipid profile, ii) serum free fatty acid and lipoprotein cholesteryl ester fatty acid profile, iii) apolipoprotein profile, iv) serum paraoxonase activities, serum paraoxonase genotype and C-reactive protein level, and v) serum oxysterol profile.

**Specific Aim 2 >** Investigate the associations if any, between the observed changes in lipid profile in Aim 1 and fatigue outcomes. Identify the lipid profile biomarkers that are most strongly associated with fatigue outcomes in MS. Assess whether these lipid profiles changes are potential mediators of the effects of diet on fatigue.

When successfully completed, this project will identify and characterize important molecular mechanisms that could explain the pathophysiological impact of the cholesterol pathway on MS fatigue. The findings can be leveraged for targeting therapeutic and lifestyle-based intervention strategies to reduce fatigue in MS patients.

- 1. State the hypotheses to be tested, if applicable.

NOTE: A hypothesis is a specific, testable prediction about what you expect to happen in your study that corresponds with your above listed objectives.

Response:

**Hypothesis 1 >** The Wahls’ Elimination Diet is associated with significant improvements in the lipid profile including decreased total cholesterol, decreased low density cholesterol (LDL-C) and apolipoprotein B (ApoB) and increases in high density cholesterol (HDL-C), decreases in cholesteryl esters conjugated with saturated fatty acids and decreased CRP levels. The Wahls’ Elimination diet increases 24-hydroxycholesterol (24HC) and decreases 7-ketocholesterol (7KC) levels.

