**Hypothesis 2 >** The improvements in the lipid profile are mediators of benefits of the Wahls’ Elimination Diet on fatigue. Subjects with greater improvements in their lipid profile will exhibit greater improvements in fatigue outcomes.

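### Hypothesis 2 and Aim 2 are about mediation, but the only stated biomarker-fatigue analysis is association regression, so parallel change or a shared cause could be read as mediation

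*Protocol*

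**What the plan says.** Under Objectives, Hypothesis 2 reads "The improvements in the lipid profile are mediators of benefits of the Wahls’ Elimination Diet on fatigue". The next sentence gives it a testable form: "Subjects with greater improvements in their lipid profile will exhibit greater improvements in fatigue outcomes". Specific Aim 2 is softer: "Assess whether these lipid profiles changes are potential mediators of the effects of diet on fatigue".

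Data Management and Analysis is where the protocol sets out its statistical procedures. Its one sentence linking biomarkers to fatigue is "Appropriate regression analyses will be used for assessing associations of cholesterol biomarker and the clinical and fatigue variables (dependent variables". On adjustment it says "The repeated measures regression analyses will adjust for age and sex because cholesterolemia risk increases with age and is more frequent in males", and of BMI that "cholesterol profiles depend on body mass index (BMI), which we will adjust for". It does not say whether BMI is taken before or after the diet starts. It adds "We will also explore other covariate adjustments", and says that the parent study's primary-outcome framework will generally be followed where suitable. The section does not mention mediation, an indirect effect, the order of biomarker and fatigue measurement, or a diet or visit term in the fatigue model.

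Study Design describes four visits 12 weeks apart. A usual-diet lead-in runs to Visit 2 (Week 12), when patients are randomised to Swank or Wahls' Elimination, with follow-up at Weeks 24 and 36. Usual diet is therefore an earlier period, not a concurrent arm. Objectives also brings in a completed multimodal study of 20 patients, compared at baseline and 12 months, and describes no control group for it.

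**The concern.** A mediation claim says that the diet changes lipids and that this change in turn changes fatigue. The stated criterion, greater lipid improvement going with greater fatigue improvement, is a correlation of changes. The same correlation can arise in two other ways:

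- **Parallel effects.** The diet, or simply the start of the intervention phase, moves both measures by separate routes. This is plausible here. Every randomised patient changes diet at the same visit, with dietitian training and coaching calls, and fatigue is measured by questionnaire.
- **A shared cause.** Something that differs between patients, such as how closely they follow the diet, drives both changes.

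If either is read as mediation, the study could name lipid biomarkers as the route by which diet relieves fatigue when no such route exists. Objectives says the findings may be used to target therapeutic and lifestyle interventions, so the distinction matters.

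**Working it through.** The protocol gives no sample size for the randomised study, no alpha and no effect size, so it has no figure to reproduce. All inputs below are assumptions except the four visits and the n = 20 of the multimodal study. The true biomarker-to-fatigue effect is zero throughout. Tests are two-sided at a nominal 0.05 with age, sex and BMI-type covariates, and shifts δ are in SD units of the measure.

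**1. Four-visit levels model, no visit or arm term.** Take two visits before and two after diet start, within-person correlation ρ = 0.6, and both measures shifting by δ in both arms. Generalised least squares weights within-person deviations by 1/(1−ρ) = 2.5 and person means by 1/(1+3ρ) = 0.357. Per patient:

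- The within-person cross-product created by the shift is 4 × (δ/2)² = δ².
- The within-person sum of squares of the biomarker is 3(1−ρ) + δ² = 1.2 + δ².
- The between-person part adds (1+3ρ) × 0.357 = 1 to the denominator and nothing to the numerator.

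So the expected slope is 2.5δ² / (4 + 2.5δ²), its standard error is 1/√[n(4 + 2.5δ²)], and z = 2.5δ²√n / √(4 + 2.5δ²). The rejection rate is Φ(z − 1.96) + Φ(−z − 1.96).

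| δ | n | z | Formula | Simulation |
|---|---|---|---|---|
| 0.3 | 40 | 0.69 | 11% | 11% |
| 0.3 | 60 | 0.85 | 14% | 14-15% |
| 0.3 | 100 | 1.09 | 19% | 19-20% |
| 0.5 | 40 | 1.84 | 45% | 42-47% |
| 0.5 | 60 | 2.25 | 61% | 56-61% |
| 0.5 | 100 | 2.91 | 83% | 78-83% |

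If only one arm shifts, by 0.8 SD, a visit term alone leaves 27-58%. With visit, arm and visit × arm the simulated rate is 4-6%.

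**2. Pre/post levels model, no time term.** With two time points, correlation 0.5 and a cluster-robust error, the rate for n = 40 to 100 is 7-13% at shifts of 0.3-0.5 SD. At 0.8 SD it is 29%, 43% and 51% for n = 40, 80 and 100. A time term brings these to 6-8%. At n = 20 the rate is about 10% even with the time term, so part of any excess there is small-sample error.

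**3. Change-on-change, no arm term.** This is the form that the second sentence of Hypothesis 2 describes.

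- *Common shift.* Adding the same constant to every patient's change leaves the correlation of changes at zero. Simulation gives 3-6%.
- *One arm shifts.* With ρ = 0.6 the change has variance 2(1 − 0.6) = 0.8. A shift of δ in half the patients adds δ²/4 to both variances and to the covariance, so r = (δ²/4)/(0.8 + δ²/4). For δ = 0.8, r = 0.16/0.96 = 0.167. With z = atanh(r)√(n − 6), allowing for three covariates, z is 0.98 at n = 40 and 1.63 at n = 100, giving 17% and 37%. Simulation also gives 17-37%. For δ = 0.5, r = 0.0625/0.8625 = 0.072 and simulation gives 6-11%. For δ = 0.3 it gives about 5%.
- *Other scaling.* If the shift is expressed in SDs of the change itself, the 0.8 SD case gives 13%, 22% and 27% for n = 40, 80 and 100.

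**4. Shared cause, arm in the model.** Let an unmeasured factor load 0.5 on each change, with residual SD 1. Then r = 0.25/1.25 = 0.20. Simulated rates are 11-12%, 21-22%, 40-42% and 49-51% for n = 20, 40, 80 and 100. An arm term does not remove this.

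**The case against.** The strongest reply is that this is detail for a statistical analysis plan, which is not shown, and that the protocol does not fix a wrong model. Much of that stands. An unseen plan may contain a mediation model. But the protocol states the mediation claim and also the criterion for it, a correlation of improvements, and that criterion does not answer the claim whatever detail follows.

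A reader might infer three stronger things that the documents do not support.

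- *That adjustment is limited to age, sex and BMI.* It is not. Other covariates are to be explored and the parent study's framework is generally adopted, so diet and visit terms are unstated rather than excluded. Neither statement commits to them, and a framework for the parent's primary outcome is not thereby a mediation analysis.
- *That any two measures that move after diet start will look like mediation.* They will not. Change-on-change regression stays near 5% under a common shift. The high rates belong to a levels model, which the repeated-measures wording allows but does not require.
- *That mediation is the study's headline claim.* Scientific Endpoints gives associations as the primary goals, the primary analysis is of 24HC and 7KC change by diet group, and Aim 2 says only potential mediators.

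The rates above are also nominal and per test. The planned Benjamini-Hochberg correction would change them by an amount that cannot be computed, because no level or family of tests is stated. It controls chance findings and does not remove bias.

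**Conclusion.** The mismatch between hypothesis and stated analysis is real. Hypothesis 2 asserts mediation, the stated analyses are associational, and parallel changes or a shared cause could be read as mediation.

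How often this would mislead is not a single number. Under the assumed n of 40 to 100 it runs from about 5% (change-on-change, common shift), through 7-20% (levels models at 0.3 SD, or pre/post at 0.5 SD), to 42-83% (four-visit levels model at 0.5 SD). Change-on-change becomes materially unsafe mainly when one arm shifts by about 0.8 SD. A shared cause of the assumed strength leaves about 11-51% for n = 20 to 100 even with arm in the model. The sample sizes, shifts, correlations and loading are assumptions; the direction of the problem does not depend on them. The point should be settled before the Aim 2 analysis begins.

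**What to change.** In Data Management and Analysis, for Aim 2:

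- **(a) Association models, randomised study.** Include visit, arm and visit × arm in the fatigue-on-biomarker models. Separate each biomarker into its person mean and within-person deviation, and test the within-person (change) term.
- **(b) Mediation.** Keep the word mediator for an analysis with randomised arm (Elimination versus Swank) as exposure, an earlier post-randomisation biomarker as mediator, and Week 36 fatigue as outcome. Week 24 suits the mediator if samples exist; the protocol does not give the blood-draw schedule. Adjust for Visit 2 biomarker, Visit 2 fatigue and pre-randomisation covariates including Visit 2 BMI. Report an interval for the indirect effect and a sensitivity analysis for unmeasured mediator-outcome confounding, because visit and arm terms do not deal with a shared cause. Do not adjust routinely for adherence or BMI measured after randomisation, since the diet can affect both. State that the contrast is with Swank, not with usual diet.
- **(c) Otherwise.** Report association only and reword Hypothesis 2 to match. This applies in any case to the 20-patient multimodal study, for which no control group is described.

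The cost is a few model terms and one further analysis with its sensitivity analysis. It needs no new patients, though Procedures Involved says the second study is still running, so its samples and data are not yet all in hand. The downside is wider intervals and fewer nominally significant associations.
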